# Effects of a Behavioral Intervention using Biofeedback on Myocardial Blood Flow Changes during Mental Stress in Patients with Coronary Artery Disease

## Study Protocol

### **Abstract:**

Psychological stress has been implicated in the pathophysiology of coronary artery disease (CAD). Myocardial ischemia can be induced by a standardized psychological challenge in some patients with CAD. This mental-stress induced myocardial ischemia (MSI) may only be provoked by a psychological stimulus rather than exercise stress. Although it is a predictor of poor prognosis, the exact mechanisms underlying MSI are unknown. One primary proposed mechanism is reduced coronary perfusion secondary to microvascular constriction that may be a result of endothelial dysfunction. Thus, assessing myocardial blood flow during mental stress would be valuable in evaluating the coronary vascular responses to psychological stress – we call this change with stress the mental stress-induced myocardial flow reserve (MS-MFR). PET measurements of myocardial blood flow (MBF) using Rb are well-established techniques. Peripheral arterial tonometry (PAT) measures digital microvascular tone and vasomotor changes during stress. Changes in the fingertip may mirror coronary vascular responses and help to gain insight on the microvascular responses during stress. Heart rate variability (HRV) biofeedback is known to improve both psychological and physiologic well-being. Previous studies have found HRV biofeedback techniques to improve mood, reduce cortisol, increase baroreflex gain, and reduce blood pressure. Whether the beneficial effects of biobehavioral therapy on autonomic tone and vascular function will improve coronary and peripheral blood flow during mental stress has not been previously evaluated and is the aim of our proposal.

In this pilot study, we will enroll 24 patients with CAD to be randomized 1:1 to HRV biofeedback therapy or waitlist control. Patients with known mental stress ischemia based on our previous study, “Mental Stress Ischemia: Genetic Mechanisms and Prognosis,” (MIPS, IRB 35540) will be recruited preferentially. All patients will undergo myocardial flow/perfusion imaging with Rb PET imaging at rest and after a standardized arithmetic mental stress test. They will then undergo repeat testing after 6 weeks. At 12 weeks, they will also undergo a limited examination without myocardial perfusion imaging. The intervention group will receive biofeedback after enrollment, and the wait-list control group will receive the intervention between the 2nd (6 week) and 3rd (12 week) study visit (without imaging). For secondary outcomes, we will also evaluate peripheral vascular function including (a) endothelial function as flow-mediated vasodilation, (b) arterial stiffness, and (c) PAT. Finally, autonomic function will be measured, including high frequency (HF) HRV (parasympathetic), pre-ejection period (sympathetic), and plasma catecholamines (sympathetic).

The aims of the study are to assess the effects of HRV biofeedback (versus usual care) on 1) MS-MFR (primary); 2) peripheral vascular function (secondary); and 3) autonomic changes during mental stress (secondary).

## **Introduction and Background**

There is growing recognition of the detrimental effects of psychological and emotional stress on coronary heart disease (CHD) incidence and mortality. Psychological stress has been implicated in the pathophysiology of CHD by triggering acute coronary events, exacerbating CHD risk factors, influencing development of atherosclerosis, and impairing the recovery, prognosis and quality of life of patients after an acute coronary syndrome. In up to half of patients with CHD, myocardial ischemia can be induced by a standardized psychological challenge. This mental-stress induced myocardial ischemia (MSI) is analogous to exercise stress ischemia, except that the stimulus is psychological rather than physical or pharmacological stress. It is typically painless, occurs at lower levels of oxygen demand than exercise ischemia, is generally not related to severity of coronary artery disease (CAD), and is a predictor of poor prognosis. However, the exact mechanisms underlying MSI and its adverse prognostic significance are unknown. One proposed mechanism is reduced coronary perfusion secondary to impaired vasodilation of the coronary circulation during mental stress that may primarily be an abnormality of the coronary microcirculation. Patients with CAD who develop MSI appear to be especially vulnerable to psychological stress and thus represent an ideal group to study the effects of intervention on myocardial perfusion changes during psychological stress.

Peripheral or pulsatile arterial tonometry (PAT) is a vascular test developed to evaluate digital microvascular vasodilator function in the fingertip. PAT reactive hyperemia predicts short and long term risk of cardiovascular events. We have shown that patients with CAD who do not develop MSI during laboratory psychological testing have significantly greater digital vasodilation, measured using PAT, than patients with MSI.

Evaluating myocardial perfusion is receiving growing attention in the assessment of the pathophysiological processes underlying myocardial response to psychological stress. PET measurements of myocardial blood flow (MBF) and myocardial flow reserve (MFR) using Rb are well-established techniques, both in research protocols and clinically. Arrighi *et al.* reported blunted augmentation of MBF, as measured by [N] ammonia PET, during mental stress in regions without significant epicardial stenosis, suggesting a prominent role for microvascular dysfunction. Thus PET is ideal for measuring mental stress-induced flow impairment due to either epicardial and/or microvascular disease.

Even though there is evidence of the significance of psychological stress on CHD pathophysiology, there is a dearth of effective behavioral interventions to mitigate the adverse effects of stress in CHD patients. Earlier studies of behavioral or psychological interventions have reported beneficial effects. In particular, stress management techniques reduce depressive symptoms, improve endothelial function measured as flow-mediated dilation, improve left ventricular ejection fraction responses to stress, and improve risk of cardiac events. More recently, Linden *et al.* performed a meta-analysis on the effect of psychological treatments in cardiac patients. Mortality benefits were reported with the addition of psychological treatments to usual care, especially when started early after an acute event. However, it was unclear as to which intervention was most likely to benefit.

In this pilot study in patients with CAD, we will use Rb PET to measure myocardial blood flow (MBF) before and after six weeks of heart rate variability (HRV) biofeedback. HRV biofeedback combines deep breathing, mindfulness, and cognitive therapy, and has been found to improve depressive symptoms and autonomic function, and has a high likelihood of success in this patient population.

## Objectives

### *Primary Objective*

Study the effects of a 6-week behavioral intervention using biofeedback (versus usual care) on global MBF and MFR during mental stress. **We hypothesize that patients who undergo a biofeedback intervention (vs. wait-listed controls) will have an increase in global and regional myocardial perfusion during mental stress (measured as RbPET MBF).**

### *Secondary objectives*

1. Study effects of biofeedback therapy on myocardial perfusion. **We hypothesize that the number of ischemic regions will decrease.**
2. Study the effects of biofeedback on peripheral vascular changes and biomarkers of sympathetic nervous system activation during mental stress. **We hypothesize that compared to controls, patients who undergo biofeedback (vs. usual care) will have less vasoconstriction (higher PAT ratio), lower resting catecholamine levels (norepinephrine, epinephrine and dopamine), and a reduced catecholamine stress response post-intervention vs. pre-intervention.**
3. Assess the relationship between stress-induced digital blood flow changes (PAT ratio), catecholamine increases, and changes in MBF before and after biofeedback intervention. **We hypothesize that compared to controls, patients with biofeedback therapy will have greater improvement in PAT ratio and lowest increases in catecholamines compared with baseline (pre-intervention).**
4. Assess the relationship between stress-induced endothelium dependent flow-mediated dilation (FMD) and arterial compliance (augmentation index and pulse wave velocity) and changes in MBF before and after biofeedback intervention. **We hypothesize that compared to controls, patients with biofeedback therapy will have greater improvement in FMD and arterial compliance.**

[figure not shown]

## Study Design and Methods

### Overall Study Design

This pilot-study (Figure 1) will recruit 24 patients from the Mental Stress Ischemia Mechanisms and Prognosis Study (MIPS), a longitudinal cohort study which enrolled 695 patients between July 2009 and July 2014 with a diagnosis of stable CAD from Emory University-affiliated hospitals or clinics. Each patient completed baseline myocardial SPECT imaging, as well as psychosocial, hemodynamic and microvascular assessments, and blood was obtained for inflammatory, neurohormonal, and immunological biomarkers prior, during and after mental stress and conventional (exercise or pharmacological) stress. These patients have been followed on regular intervals with in-person clinic visits every year and by telephone every 6 months.

The patients will be randomized 1:1 to HRV biofeedback intervention for 6 weeks or wait-list control. Each group will undergo a rest/stress Rb PET imaging protocol (detailed below) similar to regular clinical imaging except that stress will be performed with a standardized

arithmetic mental stress test rather than pharmacological stress. We will hold beta-blockers for 48 hours and calcium channel blockers and nitrates on the day of the testing. It is standard protocol to hold anti-ischemic medications, including beta-blockers, ace-inhibitors, calcium channel blockers and nitrates, before exercise stress imaging studies, and this is the protocol followed by other nuclear cardiology studies.

Figure 2: Protocol

[figure not shown]

The full protocol is detailed in Figure 2.

**Before Mental Stress Testing:** Patients will be studied in the morning after an overnight fast. After consent, patients will have 20 ml blood drawn for measurements of catecholamine levels, and inflammatory markers. They will be outfitted with a combined ECG/ICG monitor, the VU AMS holter, which is a 5-lead recorder that measures cardiac impedance and ECG for the autonomic measures. Additionally, they will measure a fitness bracelet, the Empatica E4, to measure photoplethysmography and actigraphy. In a quiet temperature controlled Vascular Laboratory, after at least 15 minute rest period, we will measure arterial compliance (augmentation index and pulse wave velocity) using the SphygmaCor device. Immediately following this, patients will be fitted with the tonometry device (PAT, Itamar Inc), and we will measure endothelial function by brachial artery reactivity testing and simultaneously also measure PAT reactive hyperemia index. Once this test is completed within 15 to 20 minutes, patients will be moved to the PET laboratory for a 30-minute rest period before the mental stress test. During this period, heart rate and blood pressure will be measured at every 5 minutes (automatic oscillometric device (Datascope Accutorr) and a continuous recording of microvascular finger blood flow using the PAT device will continue. They will continue to wear the VU AMS device and Empatica bracelet, and also undergo additional 12-lead ECG monitoring during the stress to evaluating for arrhythmia/ST changes. The resting study

Rubidium^82 infusion and PET image acquisition will be obtained approximately 7.5 mins prior to mental stress. 30-60 mCi of Rubidium^82 (based on patient body weight) will be injected in total.

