### **Mental Stress Protocol**

Mental stress will consist of a 3-min math serial subtraction paradigm previously described by Soufer et al. The subjects will be asked to serially subtract 7 from number specified (i.e., 986) by the researcher; for patients who have difficulty with this task, easier serial subtraction will be provided for (e.g., by 4, 3, or 2). Throughout the task, to increase stressfulness and titrate difficulty, the patient will be prompted for faster performance and the starting number from which they were subtracting will be periodically changed (e.g., if the starting number was 986, it may be changed to 549 after performing a number of successful serial subtractions). Finally, to add an evaluation component, patients will be given negative feedback during the test. Blood pressure and heart rate will be recorded at 1-minute intervals. Subjective stress levels will be evaluated by the use of a visual analog scale; this will be repeated at the end of the stress test. At 60 seconds into the mental stress task, 30-60 mCi of Rubidium^82 (based on patient body weight) will be injected; images will be acquired as described below.

**Post mental stress testing:** Heart rate and blood pressure will be measured every minute for the first 5 minutes and at 5 minute intervals after the end of the mental test. Microvascular blood flow will also be continuously measured by PAT. Five minutes after the end of the test, 20 ml of blood will be drawn for catecholamine levels. Fifteen minutes after the mental stress test, arterial compliance measures will be repeated. Thirty minutes after the end of the test, brachial reactivity and simultaneous PAT reactive hyperemia will be repeated and the PAT device disconnected. Ninety minutes after stress, another 20 ml sample of blood will be drawn for future studies involving post-stress inflammatory measures, determined at a later date.

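### The pre-stress catecholamine sample, used as both resting level and stress-response reference, is drawn right after consent, with no rest specified and at least 60 minutes before the task

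*Protocol*

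**What the plan says.** The Protocol describes the visit in sequence under Overall Study Design. The first procedure is the blood draw: "After consent, patients will have 20 ml blood drawn for measurements of catecholamine levels, and inflammatory markers". Monitor fitting comes next. Then, "after at least 15 minute rest period, we will measure arterial compliance". Brachial reactivity and the reactive hyperemia index follow, with 15 to 20 minutes given for that test. After it, "patients will be moved to the PET laboratory for a 30-minute rest period before the mental stress test". For that last rest the text lists heart rate and blood pressure ("During this period, heart rate and blood pressure will be measured at every 5 minutes"), continuous PAT recording and the rest PET scan, but no blood draw.

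Under Mental Stress Protocol the post-stress sample is fixed: "Five minutes after the end of the test, 20 ml of blood will be drawn for catecholamine levels". The Blood tests paragraph and the Autonomic Measurements section restate the scheme only as before and after stress. Neither adds a second pre-stress sample nor attaches a rest condition to the one described. Blood tests also says that all visits follow the same protocols.

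Secondary objectives, item 2, hypothesises "lower resting catecholamine levels (norepinephrine, epinephrine and dopamine), and a reduced catecholamine stress response post-intervention vs. pre-intervention". Item 3 relates catecholamine increases to PAT ratio and to changes in myocardial blood flow.

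**The concern.** Both catecholamine hypotheses in item 2 depend on this one sample. It is the resting level, and it is the value subtracted to obtain the stress response. As written, no rest is required before it, and more than an hour of other procedures separates it from the post-stress sample. The pre-to-post change therefore spans a cuff occlusion, a move between laboratories and a 30-minute rest as well as the 3-minute task.

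The other baselines are treated differently. Arterial compliance follows at least 15 minutes of rest, brachial dilation at least 10 minutes supine, and the hyperemia index a 10-minute equilibration. Heart rate, blood pressure and PAT are recorded through the final rest, and the rest scan is acquired near its end. Item 3 would therefore correlate a catecholamine change with PAT and flow changes that start from a different reference state. In a pilot of 24 patients, added noise in a change score is costly, and it cannot be removed once the samples are collected.

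**Working it through.** **Inputs, all from the Protocol**
- First rest: at least 15 min (Overall Study Design).
- Brachial and hyperemia test: 15 to 20 min (same section). The components given for the hyperemia index are 10 min equilibration + 5 min occlusion + 5 min recording = 20 min, which agrees with the upper figure.
- PET-room rest: 30 min (same section).
- Rest tracer infusion and scan: about 7.5 min before stress (same section).
- Task: "Mental stress will consist of a 3-min math serial subtraction paradigm", so 3 min.
- Post-stress draw: 5 min after the task (Mental Stress Protocol).

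Monitor fitting, the arterial compliance measurement and the transfer have no stated duration and are counted as zero, so the pre-stress intervals are lower bounds. The Protocol states no draw-to-task interval of its own to reproduce.

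**Intervals as written**
- Draw to task: 15 + 15 + 30 = 60 min, or 15 + 20 + 30 = 65 min.
- Draw to post-stress sample: 60 + 3 + 5 = 68 min, or 65 + 3 + 5 = 73 min.
- Draw to rest scan: 60 − 7.5 = 52.5 min, or 65 − 7.5 = 57.5 min. This is the mismatch in item 3 between the catecholamine and flow baselines.

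**Intervals if the sample is moved**
- Start of rest infusion to post-stress sample: 7.5 + 3 + 5 = 15.5 min. With the draw a few minutes before the infusion, the span is about 16 to 20 min.
- A draw at the very end of the rest would give 3 + 5 = 8 min, but it would fall during the rest scan.

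**Effect on the response**

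Let R be the rested level, E any excess at the early draw and S the post-stress level. The measured response is S − (R + E) = (S − R) − E.
- If E is the same in both arms and at both visits, it cancels from the comparison of mean changes. Its within-patient variation remains as noise.
- If training removes a fraction f of E by week 6, with no matching fall in S, the biofeedback arm's measured response rises by f × E, against the hypothesis.

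The Protocol gives neither E nor f. Purely as an assumption, take E = 20% of the resting level. The shift is then 0 for f = 0, 10% of the resting level for f = 0.5 and 20% for f = 1. If E is zero, the shift is zero whatever f is. These figures show direction only and do not estimate the likely size.

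**The case against.** A reader might infer that the sample is taken on arrival and is known to be unrested. The text does not say so. It places the draw after consent and is silent on rest beforehand. Consent is given at entry to the study, so that wording does not by itself fix the draw time at week 6, although the statement that all visits follow the same protocols suggests the order carries forward. Figure 2, said to hold the full protocol, is not visible, so a later resting draw cannot be excluded. If the figure shows one, it conflicts with the text.

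A reader might also infer that neither hypothesis can be tested, or that the week-6 comparison is biased against biofeedback. Neither follows. The sample is a morning, fasting, pre-task value, and the hypotheses compare randomised arms, so a shift common to both arms cancels. Differential bias needs three unsupported steps: a raised value at the draw, training that lowers it, and no corresponding fall after stress. Moving the draw would not remove that possibility altogether. The Protocol itself hypothesises lower resting levels, and a lower baseline raises any change score wherever it is drawn.

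The impact is also limited. Pre-ejection period and PAT capture sympathetic and vascular responses without this sample. A draw close to the rest scan could disturb the denominator of the primary outcome, and the Protocol does not say that the intravenous catheter can be used for sampling.

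These points limit the claim, but they leave the stated sampling order, the interval and the lack of any described rest condition as they are.

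**Conclusion.** The point holds as a mismatch between sampling time and hypothesis. The only pre-stress catecholamine draw described comes at least 60 to 65 minutes before the task, ahead of both rest periods, yet it serves as the resting level and as the reference for the stress response. The expected result is a noisier and probably shifted reference for the catecholamine outcomes, and a reference state in item 3 that differs from that of PAT and blood flow. A between-arm bias at week 6 is possible but cannot be sized from the Protocol. The primary outcome, MS-MFR, is unaffected. The conclusion rests on the visible text being complete on this point, since Figure 2 is not shown, and on the listed order being the order carried out. The change is worth making because it is cheap and the analysis cannot recover a rested sample later.

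**What to change.** At each imaging visit, take the pre-stress catecholamine sample late in the 30-minute PET-room rest, a few minutes before the rest Rb-82 infusion, through the venous line placed for the tracer. Use this sample for both the resting level and the stress response. The inflammatory sample can stay where it is. Bring Figure 2, the pre-test paragraph, Blood tests and Autonomic Measurements into line with this time, and state the draw time and rest condition for the 12-week visit as well. In the same edit, reconcile the post-stress time, which Blood tests calls immediate and Mental Stress Protocol puts at five minutes.

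The cost is a small change in visit order and possibly one extra tube if the inflammatory draw stays early. The line must be in place beforehand and must allow sampling, so that no fresh needle stick precedes the rest scan.

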### **Mental Stress Protocol**

Mental stress will consist of a 3-min math serial subtraction paradigm previously described by Soufer et al. The subjects will be asked to serially subtract 7 from number specified (i.e., 986) by the researcher; for patients who have difficulty with this task, easier serial subtraction will be provided for (e.g., by 4, 3, or 2). Throughout the task, to increase stressfulness and titrate difficulty, the patient will be prompted for faster performance and the starting number from which they were subtracting will be periodically changed (e.g., if the starting number was 986, it may be changed to 549 after performing a number of successful serial subtractions). Finally, to add an evaluation component, patients will be given negative feedback during the test. Blood pressure and heart rate will be recorded at 1-minute intervals. Subjective stress levels will be evaluated by the use of a visual analog scale; this will be repeated at the end of the stress test. At 60 seconds into the mental stress task, 30-60 mCi of Rubidium^82 (based on patient body weight) will be injected; images will be acquired as described below.

**Post mental stress testing:** Heart rate and blood pressure will be measured every minute for the first 5 minutes and at 5 minute intervals after the end of the mental test. Microvascular blood flow will also be continuously measured by PAT. Five minutes after the end of the test, 20 ml of blood will be drawn for catecholamine levels. Fifteen minutes after the mental stress test, arterial compliance measures will be repeated. Thirty minutes after the end of the test, brachial reactivity and simultaneous PAT reactive hyperemia will be repeated and the PAT device disconnected. Ninety minutes after stress, another 20 ml sample of blood will be drawn for future studies involving post-stress inflammatory measures, determined at a later date.

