### **PET Imaging Protocol**

All studies will be acquired using a Siemens Biograph-40 3D PET/CT scanner (Knoxville, TN) comprised of a lutetium oxyorthosilicate (LSO) block detector ring of 162 mm field-of-view operating in 3D mode.

Images are acquired as follows: a scout is done to define scan range. A CT attenuation scan is performed with the lowest pitch allowed by the scanner, covering the region of interest in 14 seconds during shallow breathing. Two rubidium infusions of 1295 – 2220 MBq (35-60 mCi) are performed. A 7.5-minute rest emission scan in list mode is started immediately after the beginning of rubidium infusion. Mental stress is then performed using the subtraction paradigm described above, and the rubidium generator is started immediately after mental stress is completed. A 7.5-minute stress emission scan in list mode is started immediately after the beginning of rubidium infusion. Lastly, for approximately ½ the patients, pharmacologic stress with Regadenason 0.4 mg will be performed as well, followed by a 3rd 7.5 minute stress. Manual rigid-body registration of the CT and PET images is performed by using manufacturer-provided software.

**Static Reconstruction.** The diagnostic images will be reconstructed using ordered-subsets expectation maximization (OSEM) algorithm (4 iterations, 16 subsets) with a Gaussian post-

filter of 7 mm. A standard 2-minute delay will be applied to the list mode data for final attenuation correction static reconstruction.

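### The protocol gives two incompatible start times for the mental-stress rubidium infusion, one during the task and one after it, so the stress flow in the primary endpoint is not uniquely defined

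*Protocol*

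**What the plan says.** Four places in the protocol bear on when stress flow is measured.

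- **Mental Stress Protocol.** The task is fixed in length: "Mental stress will consist of a 3-min math serial subtraction paradigm". The stress rubidium is injected "At 60 seconds into the mental stress task", and the reader is then sent on to the imaging text: "images will be acquired as described below".
- **PET Imaging Protocol.** This is the text referred to. It says that "the rubidium generator is started immediately after mental stress is completed", and ties the scan to the infusion: "A 7.5-minute stress emission scan in list mode is started immediately after the beginning of rubidium infusion".
- **Primary Objective.** The effect of interest is "on global MBF and MFR during mental stress", and the hypothesis is an "increase in global and regional myocardial perfusion during mental stress".
- **Abstract.** All patients have PET "imaging at rest and after a standardized arithmetic mental stress test".

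**The concern.** The primary outcome is the mental-stress myocardial flow reserve (MS-MFR), which compares stress flow with rest flow. The protocol fits flow to time-activity curves from a scan that starts with the infusion, so the moment of infusion determines which physiological state the stress value represents. An infusion during the task captures flow under the stressor. An infusion after it captures flow once the stressor has been removed.

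Two things are at stake. First, if the PET Imaging Protocol is followed as written, the stress measurement lies wholly outside the period named in the Primary Objective. Second, if different operators, or the baseline and week-6 visits, follow different sections, timing error enters the within-patient change that the Statistical analysis section compares between arms. Neither problem can be repaired after scanning, because flow during a missed stress interval was never recorded.

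**Working it through.** **Do the two sections describe the same infusion?** Yes. The PET Imaging Protocol counts two rubidium infusions, one for rest and one for mental stress. It refers back to the subtraction task, and it describes the regadenoson scan (about half the patients) separately afterwards. The Mental Stress Protocol refers forward to it for acquisition. Neither timing is labelled as an option, a phase or a subgroup.

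**Inputs**
- Task length: 3 min = 180 s (Mental Stress Protocol).
- Infusion start, timing A: 60 s after task start (Mental Stress Protocol).
- Infusion start, timing B: at task end, so 180 s or later (PET Imaging Protocol).
- Scan length: 7.5 min = 450 s, starting with the infusion (PET Imaging Protocol).

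**Formula.** Scan seconds within the task = task length − infusion start, with a floor of 0. Share = that figure ÷ scan length.

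| | Timing A | Timing B |
|---|---|---|
| Seconds within the task | 180 − 60 = 120 | 180 − 180 = 0 |
| Share of scan | 120 / 450 = 26.7% | 0 / 450 = 0% |
| Seconds after the task | 450 − 120 = 330 | 450 |

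The infusion start differs by at least 180 − 60 = 120 s.

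**Why the early seconds matter.** The PET Flow Analysis section fits a kinetic model to the time-activity curves and reads K1, the rate of tracer transfer from blood to tissue, as flow times extraction. The 120 s of overlap under timing A are the first 120 s of the scan and include initial tracer delivery. The late summed image (2–5 min) does not change this: it serves to place the regions of interest, which are then applied to each image to obtain the curves.

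**Which timing does the rest of the text support?** It is split. The Primary Objective, with flow during stress, agrees with timing A. The Abstract, with imaging after the test, agrees with timing B.

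**The case against.** The strongest reply is that the conflict need not do much harm. The PET section starts the infusion directly at task end, with no recovery interval. The protocol also treats some vascular effects of stress as outlasting the task: its flow-mediated dilation section places the peak loss of endothelial function at 30 minutes after stress. If one timing is used throughout, both arms are measured alike and the randomised comparison stays valid. Figure 2, said to give the full protocol, is not available here and may show the operational timing.

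Much of this stands. Consistent use of either timing would protect the comparison between arms, though under timing B it would be a comparison of a different quantity from the one in the objective. The endothelial evidence is brachial, not coronary, so it does not show that coronary flow persists after the task. A clear Figure 2 would still leave two operative sections in conflict.

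The reply also marks the limits of the point. A reader might infer that post-task imaging would bring MS-MFR to 1.0 and erase the planned difference of 1.38 − 1.1 = 0.28. The documents do not support that: it assumes complete recovery of flow before the tracer arrives, and no recovery rate is given. A reader might also infer that imaging sites will differ, but all studies use a single scanner model and recruitment is confined to one university's affiliated hospitals and clinics. The plausible variation is between operators and visits. Finally, a reader might take the 60-second timing as simply the right one. The objective favours it, but the Abstract points the other way, and the documents do not establish which was intended.

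**Conclusion.** The contradiction is real, and the text is wrong as it stands: one infusion has two start times at least 120 s apart. Scan overlap with the stressor is 120 of 450 s (27%) under one and 0 of 450 s under the other. The stress flow used in the primary endpoint is therefore not uniquely defined, and one of the two definitions does not fit the stated objective.

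The overlap figures rest only on the protocol's own times and on the scan starting with the infusion. Any resulting bias or loss of power is unquantified, since it depends on how fast flow recovers after the task. Added error in the change score is conditional on the two timings being mixed, which the text permits but does not show. The point should be settled before scanning because the primary measurement depends on it.

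**What to change.** Reconcile the Abstract, the Mental Stress Protocol and the PET Imaging Protocol to one infusion start time, expressed relative to task start, that is consistent with the Primary Objective. If post-task imaging is what the sponsor intends, restate the objective and the endpoint as post-stress flow instead. Check that Figure 2 shows the same timing.

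Apply that timing to every mental-stress scan at baseline and week 6, and record the actual infusion start relative to task start for each scan, so that departures can be seen and examined.

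The cost is a few words in the protocol and one line on the PET worksheet, with no extra scans or patients. The same two sections also give different rubidium activity ranges (30–60 and 35–60 mCi), which can be reconciled in the same edit.
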